## **8.5 Withdrawal of individual subjects**

Subjects can leave the study at any time for any reason if they wish to do so without any consequences. Subjects are instructed to return all trial materials to the study team when they decide to leave the study. The study team will also notify Ava within 5 business days of the participant's withdrawal, so the device manufacturer can remotely turn off the Ava bracelet and thus ensure no off-label use occurs.

### **8.5.1 Specific criteria for withdrawal**

A subject will be withdrawn from the study for any of the following reasons:

- Lost to follow up
- Withdrawal of consent
- Death
- If a subject is poorly compliant (< 20%) with the completion of either the daily Symptom Diary or syncing of the bracelet
- If the subject is using the Ava Bracelet for other purposes as the study purpose (for example for women to detect menstrual cycle changes among ovulation)

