#### **8.4.5 Assignment of Unique Identification code (UID) and randomization to sequence**

Following the successful signing of informed consent form, subjects will be stratified based on their demographic information provided at registration to either the normal-risk or high-risk group. In addition, they will be assigned a UID and randomized to one of the two sequences. Subjects will be blinded as to the sequence that they have been assigned to.

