#### **8.4.6 Receive starter kit**

Subjects will then receive a starter kit through the postal service. This starter kit will contain the following items: Ava bracelet, self-sampling kits for serology tests, detailed instructions on how to use the self-sampling kits, general study instructions for the Ava bracelet and Ava COVID-RED app and pre-addressed (medical) return envelopes with prepaid postage.

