## **8.7 Follow-up of subjects withdrawn from treatment**

To ensure the number of subjects lost to follow-up is kept to a minimum, the subject will be asked to provide contact details of a back-up person upon study entry. In the event that a subject is considered lost to follow-up, the investigator may decide to contact this back-up person to enquire if the subject is able to re-join the study. A specific study procedure will be available to support this process.

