#### *Analysis sets*

Several analysis sets will be defined which will be used for the analyses described in the following sections:

- **Intention-to-treat set:** All subjects randomized to one of the two study sequences. For the analysis, subjects will be considered part of the study sequence that they were originally randomized to. Note that when a subject has their first SARS-CoV-2 infection (as confirmed through a positive PCR/antigen or serology test), they will no longer be part of the analysis going forward because they have met the primary outcome.

- **Efficacy analysis set:** All compliant subjects randomized to one of the two study sequences, where compliance is defined as having entered symptom data in the Ava COVID-RED app on at least 80% of the days of Period 2 **and**, when in the experimental condition, having worn and synchronised the Ava bracelet on at least 80% of the days of Period 2.
- **Partial compliance set:** All subjects randomized to one of the two study sequences that were partially compliant; which is defined as having entered symptom data in the Ava COVID-RED app on at least 80% of the days of Period 2 **or**, when in the experimental condition, having worn and synchronised the Ava bracelet on at least 80% of the days of Period 2.
- **Safety analysis set:** All subjects who were randomized and received an Ava bracelet.

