### 10.2 Primary Analysis of Primary Endpoint(s)

The primary analysis of the primary endpoint will compare the performance of the algorithm applied in each study condition to detect if subjects were ever infected during Period 2. This analysis will be performed on both the Intention-to-treat and Efficacy analysis sets, within each period and stratified per risk group. For the subjects within each study condition, the daily prediction of possible SARS-CoV-2 infection and the results of PCR/antigen and serology tests will be summarized over the whole period per subject to determine (1) if a subject was ever judged to have a high risk for a potential SARS-Cov-2 infection (i.e. received a red-light indicator from the Ava COVID-RED app), and (2) if a subject was ever confirmed to have a SARS-CoV-2 infection by PCR/antigen or serology testing. For this comparison, parameters such as sensitivity, specificity, positive predictive value, and negative predictive value will be calculated.

To confirm whether a subject was ever infected in Period 2 with SARS-CoV-2, the serology status at the end of Period 2 for each subject still alive at that time will be used as the gold standard. Those with a previous positive test result will be excluded from the analysis. For subjects not alive at the end of Period 2, the status of available SARS-CoV-2 virus tests during Period 2 will be used (positive at any time) and for those without any test results, a physician diagnosis during Period 2 will be accepted provided there was a supportive lung CT scan used. All other subjects will be summarized for transparency but excluded from the estimation for sensitivity, specificity, positive predictive value and negative predictive value.

The following quantities are needed for these statistics:

- **Predicted condition positive:** The total number of subjects that obtained a red-light indicator from the Ava COVID-RED app at least once during Period 2.
- **Predicted condition negative:** The total number of subjects that never obtained a red-light indicator from the Ava COVID-RED app during Period 2.
- **Condition positive:** The total number of subjects who tested positive at least once using SARS-CoV-2 virus testing during Period 2 OR who had a positive serology test at the end of Period 2.
- **Condition negative:** The total number of subjects who never tested positive for the SARS-CoV-2 virus during Period 2 AND who had a negative serology test at the end of Period 2.

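### Subjects withdrawn after randomisation for under 20% compliance have no provision for end-of-period serology, so the intention-to-treat accuracy estimates omit part of the randomised set

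*Protocol*

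**What the plan says.** - **Withdrawal rule (Protocol 8.5.1).** "A subject will be withdrawn from the study for any of the following reasons", and one reason listed is "If a subject is poorly compliant (< 20%) with the completion of either the daily Symptom Diary or syncing of the bracelet". The withdrawal is from the study, not only from the device or app. No time window is given, and the rule is the same in both conditions.
- **Randomisation (8.4.5).** At enrolment, before any diary or bracelet data exist, "they will be assigned a UID and randomized to one of the two sequences".
- **Follow-up of withdrawn subjects (8.7).** The only provision is recontact: "In the event that a subject is considered lost to follow-up, the investigator may decide to contact this back-up person". Nothing covers serology after withdrawal for poor compliance.
- **Intention-to-treat set (section 10, Analysis sets).** "All subjects randomized to one of the two study sequences".
- **Reference standard (10.2).** For Period 2, "the serology status at the end of Period 2 for each subject still alive at that time will be used as the gold standard". Virus tests or a CT-supported diagnosis may stand in for subjects who have died. Everyone else is described but left out of the four accuracy measures.
- **Completeness (8.4.8).** The protocol expects almost complete knowledge of infection status at the end of each period.
- **Starter kit (8.4.6).** It already contains "self-sampling kits for serology tests".

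**The concern.** Put together, these rules create a post-randomisation exclusion linked to the result being estimated. Section 10.2 counts anyone who never received a red light as predicted negative. Someone who enters almost no diary data has few chances to receive one, so an infected subject of this kind will often be a false negative. Withdrawal, as the rule reads, removes that subject's end-of-period sample and with it the false negative.

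Two things are at stake. First, the intention-to-treat estimates no longer describe all randomised subjects, although section 3.7 says the interest lies in performance in a real-world setting, where non-use is part of performance. Secondly, the rule conflicts with the protocol's own analysis sets, because it withdraws people whom those sets are defined to include.

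**Working it through.** **1. Does the loss follow from the text?** Randomisation precedes all compliance data, so every compliance withdrawal is post-randomisation. Because 8.5.1 sets no window, poor compliance in the Learning Phase or Period 1 can remove a subject before Period 2, the primary evaluation period. A living subject without an end-of-Period-2 result falls into the group that 10.2 excludes from estimation. There is one inconsistency: the condition-positive definition in 10.2 accepts a positive virus test in Period 2 alone, whereas the reference-standard paragraph relies on serology for the living. Even on the wider definition, an untested infection in a withdrawn subject is lost, and the condition-negative definition still requires a negative serology result.

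**2. Whom does the rule remove?**

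| Subject | Effect on the alert | Status under section 10 |
|---|---|---|
| Little diary data, control | few or no alerts (algorithm uses symptoms and background data, 8.4.11) | infected: likely false negative |
| Little diary data, regular syncing, experimental | alert still possible from physiology (3.4) | can meet Partial compliance |
| Diary at least 80%, syncing under 20%, control | none | meets the Efficacy definition |
| Diary at least 80%, syncing under 20%, experimental | mainly loses pre- or asymptomatic detection (4.4.2 has both algorithms flag symptomatic subjects together) | meets Partial compliance |

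**3. Size.** Let w be the share of infected subjects withdrawn, Se_r sensitivity in those retained and Se_w sensitivity in those withdrawn.

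- Sensitivity in all randomised = (1 − w) × Se_r + w × Se_w
- Reported sensitivity = Se_r
- Overstatement = w × (Se_r − Se_w)

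The protocol gives none of the three inputs, and there is no stated figure to reproduce. All values below are assumptions. The middle columns use Se_r = 0.80 and Se_w = 0.20. For example, at w = 5%: 0.95 × 0.80 + 0.05 × 0.20 = 0.77. The last column runs from w × (0.70 − 0.40) to w × (0.80 − 0).

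| w | All randomised | Overstatement, points | Range, points |
|---|---|---|---|
| 5% | 0.77 | 3 | 1.5 to 4 |
| 10% | 0.74 | 6 | 3 to 8 |
| 20% | 0.68 | 12 | 6 to 16 |
| 30% | 0.62 | 18 | 9 to 24 |

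**4. How much could retained follow-up recover?** If a fraction r of the withdrawn group returns a sample, and return is unrelated to alert status within that group, the estimate becomes [(1 − w) × Se_r + w × r × Se_w] / [(1 − w) + w × r]. At w = 10%, with 0.80 and 0.20:

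- r = 20%: (0.72 + 0.004) / 0.92 = 0.787, a correction of 1.3 points
- r = 50%: (0.72 + 0.01) / 0.95 = 0.768, a correction of 3.2 points
- r = 100%: 0.74, the full 6 points

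**5. Difference between conditions.** With E for experimental and C for control, the bias is w_E × (Se_r,E − Se_w,E) − w_C × (Se_r,C − Se_w,C). Low diary use with regular syncing can leave a smaller gap in the experimental condition. Low syncing with a full diary leaves a gap only there. These push in opposite directions, so the sign is not determined.

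**The case against.** The case against has several sound parts.

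- **Loss of serology is inferred.** No sentence says that sampling stops. However, withdrawal is from the study, 8.7 offers nothing beyond recontact, and 8.5 has subjects who leave return their trial materials. The inference is reasonable, and at the least the protocol leaves the matter open.
- **Low compliance does not always mean a miss.** A reader might infer that everyone withdrawn is among those most likely to be missed. The documents do not support that: with a full diary, low syncing leaves the control alert unchanged and in the experimental condition mainly costs early or asymptomatic detection. Nor does low diary use rule out an alert. Symptoms can be entered up to 7 days late (8.4.9), one red light in the period suffices, and just under 20% of about 90 days still allows 17 entries.
- **Low compliers may not return samples anyway.** This is fair. Part of the gap would exist without the rule, as step 4 shows.
- **The retrospective within-person comparisons (10.2, 10.3) need bracelet data from everyone.** That justifies an analysis set of compliant subjects, which section 10 already has. It does not justify ending outcome collection.
- **The SAP may add imputation or sensitivity analyses.** It may, but it cannot restore samples that were never taken.

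A reader might also infer that withdrawal differs by condition and so favours one algorithm. The protocol gives no ground for this: subjects are blinded, their duties are the same in both conditions, and so is the threshold.

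**Conclusion.** The point holds in a limited form. As written, 8.5.1 together with 10.2 takes some randomised subjects out of the intention-to-treat accuracy estimates and undermines the completeness claimed in 8.4.8. It also removes subjects who can meet the Efficacy definition (control condition) or the Partial compliance definition (experimental condition).

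Each condition's own sensitivity is probably overstated, because infected subjects with little diary data are likely false negatives. The size is unknown. It would be tempting to quote 3 to 18 points as the effect of the rule, but that range uses invented sensitivities, needs the share of infected subjects rather than of all subjects, and assumes that every withdrawn subject would otherwise have returned a sample. No direction can be claimed for the comparison between conditions.

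The conclusion rests on reading withdrawal from the study as ending serology. The protocol implies this but does not say it.

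**What to change.** In 8.5.1, remove poor compliance as a reason for withdrawal from the study. Such subjects may stop the diary and bracelet and return the device, but they keep the serology kits and are still asked for the end-of-period fingerprick and the surveys. State this in 8.7, and count these subjects in the intention-to-treat analysis. Keep the two sets based on 80% compliance for analyses of compliant subjects. In 10.2, reconcile the serology rule for living subjects with the condition-positive definition that accepts a virus test alone.

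The cost is amendment wording and some extra assays, since kits are already sent at the start. Return from this group will probably be incomplete, so the bias is reduced rather than removed. The number with and without an end-of-period result should be reported by condition.

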## **8.6 Replacement of individual subjects after withdrawal**

There will be no replacement of subjects in this study.

## **8.7 Follow-up of subjects withdrawn from treatment**

To ensure the number of subjects lost to follow-up is kept to a minimum, the subject will be asked to provide contact details of a back-up person upon study entry. In the event that a subject is considered lost to follow-up, the investigator may decide to contact this back-up person to enquire if the subject is able to re-join the study. A specific study procedure will be available to support this process.

## **8.8 Premature termination of the study**

In case the study team, a Regulatory Authority or Independent Ethics Committee elects to terminate or suspend the study, a study-specific procedure for early termination is to be followed.

## 9. SAFETY REPORTING

### 9.1 Temporary halt for reasons of subject safety

The sponsor will suspend the study if there is sufficient ground that continuation of the study will jeopardise subject health or safety. The sponsor will notify the accredited EC without undue delay (within 2 working days and not later than 4 calendar days) of a temporary halt including the reason for such an action. The study will be suspended pending a further positive decision by the accredited EC. The investigator will take care that all subjects are kept informed.

### 9.2 ADEs, SADEs and USADEs

This protocol is considered a low-risk study. The Ava bracelet is a Class IIa device for which a Declaration of Conformity is available. The hardware and sensors used to measure heart rate, breathing rate, wrist skin temperature, heart rate variability, sleep duration, and skin perfusion are identical to their counterparts in the Ava's commercially available product, the Ava Fertility Tracker (<https://www.avawomen.com/how-ava-works/healthcare/technology/>). The sponsor shall be responsible for documentation, assessment and reporting all safety events including adverse device effects (ADEs), severe adverse device effects (SADEs) and device deficiencies according to local and national regulatory requirements. The sponsor shall ensure all Ava device-related safety and device deficiency information are reported to Ava's customer service for vigilance purposes.

#### 9.2.1 Adverse device effects (ADEs)

Adverse events, in general, are defined as any undesirable experience occurring to a subject during the study, whether or not considered related to the device or the study. In this trial, we will restrict the recording of adverse events to only the device related effects (ADEs) which will be reported. The subjects will be reminded regularly to report any occurring ADEs related to the (use of the) device through a survey. These ADEs will be followed up (see section 9.4) by the investigator (or delegate) and entered in the eCRF.

All ADEs will be reported to the manufacturer within 5 business days of notification from the subject.

#### 9.2.2 Serious adverse device effects (SADEs)

A serious adverse event, in general, is any untoward medical occurrence or effect that

- results in death;
- is life threatening (at the time of the event);
- requires hospitalisation or prolongation of existing inpatients' hospitalisation;
- results in persistent or significant disability or incapacity;
- is a congenital anomaly or birth defect; or
- any other important medical event that does not result in any of the outcomes listed above due to medical or surgical intervention but could have been based upon appropriate judgement by the investigator.

An elective hospital admission will not be considered a reason to consider an event serious. In this trial, we will restrict the recording of SAEs to only the device-related SAEs (SADEs). These will be reported to the manufacturer within 24 hours of receiving notification from the subject. Each SADE that may occur during the course of the COVID-RED clinical trial should be documented on the Spontaneous Adverse Event and Device Deficiency Report Form provided by the manufacturer, or on a similar form containing the same information as the form provided by the manufacturer. This form should also be completed for device deficiencies that could have resulted in a SADE under different circumstances. The Spontaneous Adverse Event and Device Deficiency Report Form must be completed in as much detail as possible, including at the minimum the device serial number and country of event. Whenever possible, pictures documenting the ADE, SADE and/or device deficiency should be included. The completed form should be sent to the following customer service support email address:

[[contact]](mailto:[contact])

Seriousness is judged by the study investigator (or delegate).

All serious adverse events that lead to (temporary) suspension/stop of the clinical trial or adjustment in the medical device and all unexpected serious adverse device reactions which indicate an imminent risk of death, serious injury, or serious illness and that require prompt remedial action for other patients/subjects, users or other persons, will be reported expedited to the CCMO and EC within 2 working days and not later than 4 calendar days.

All other serious adverse device effects will be reported quarterly to the CCMO and EC via the MEDDEV 2.7.3 form.

### 9.2.3 Unanticipated serious adverse device effects (USADEs)

Serious adverse device effects are considered unanticipated serious adverse device effects (USADEs) if the following 3 conditions are met:

- The event is serious (see the definition above)
- There is a certain degree of probability that the event is a harmful and an undesirable reaction to the medical device under investigation,
- The adverse device reaction is unexpected, i.e, the nature and severity of the adverse device reaction are not in agreement with the product information as documented in the reference information (in this study: the Investigational Medical Device Dossier [IMDD])

### 9.3 Annual safety report

Not applicable

### 9.4 Follow-up of adverse device effects

All (S)ADEs will be followed until they have abated, until a stable situation has been reached or if the Investigator (or delegate) decides that (further) follow-up of the ADE is not needed (for example in case of a relatively minor event, such as redness of the skin where the bracelet was worn). Depending on the event, follow-up may require additional tests or medical procedures as indicated, and/or referral to the general physician or a medical specialist. SADEs will always be followed up until abated or until a stable or chronic situation has been reached in the opinion of the Investigator (or delegate).

SADEs need to be reported until the end of study in the Netherlands.

### 9.5 Data Safety Monitoring Board (DSMB) / Safety Committee

Not applicable

## 10. STATISTICAL ANALYSIS

Below an overview is given regarding the planned statistical analyses for the trial. Further details as well as additional models and sensitivity analyses will be provided in a separate Statistical Analysis Plan.

### *General statistical approach*

Appropriate statistical methods will be selected for each research question depending upon the nature of the data distribution as well as the effect that is to be characterized. Categorical variables will be presented as absolute numbers and percentages, while continuous variables will be described by number of observations, mean, standard deviation, median and range (minimum and maximum). While maximum effort will be put into the minimization of missing data, the remote nature of the study and the reliance on self-reporting by the subjects might lead to the presence of missing data. Where necessary, missing data mechanisms will be investigated and imputation methods will be used or robust statistical methods such as bootstrap estimation employed. The count and percentage of known missing data will be described. Analyses and results between and within the study conditions will also be reported overall and separately for the different strata (e.g., normal-risk vs. high-risk population). Additionally, with the exception of the baseline data, all data will be analysed and reported within each period of the trial with pooling of the data only in specifically mentioned cases in the sections below. All statistical confidence intervals will be two-sided and at the 95% level. P-values, or similar measures resulting from bootstrap methods, will be considered significant if less than 0.05 with two-sided testing and if less than 0.025 with one-sided testing. No adjustments for multiplicity of tests are planned. For both the primary and secondary endpoints (where relevant), we will assess the COVID-19 vaccinated portion of the study sample as a key subset. The potential effect of COVID-19 vaccination among some subjects on the analyses of interest will be investigated using sensitivity analyses. This may include truncation of certain data occurring after vaccination events as part of these sensitivity analyses. Further details will be captured in the statistical analysis plan.

